### Data collection

We will record participant data using questionnaires on Research Electronic Data Capture (REDCap), a secure online data collection platform [44]. Study staff will administer the questionnaires in the preferred language of resident and lay health worker participants (Fig 1).

### Resident questionnaire measures

*Sociodemographics.* At baseline, we will obtain information on age, sex assigned at birth, gender identity, race/ethnicity, education, employment status, income from all sources, and length of stay in current residence.

*Social determinants of health.* We will obtain information on unmet needs [45], residential history [42,43,46], homelessness history [42,43,46], exposure to urban life stressors [47], quality of housing [25], and neighborhood safety [48,49].

*Neighborhood-level factors.* We will ask where participants obtained their tobacco products, and how far they have to travel to obtain tobacco, cannabis, and alcohol products [28].

*Alternative tobacco products and cannabis use.* We will assess lifetime and past 30-day use of e-cigarettes, cigars/little cigars, smokeless tobacco, hookah, blunts, and cannabis.

*Tobacco dependence and smoking cessation.* We will use Fagerstrom’s test for nicotine dependence [50], assess e-cigarette dependence [51], quit attempts (past year and in the past 3 months), length of the last quit attempt, and use of cessation aids [52].

*Smoke-free policy.* We will assess smoke incursion, knowledge of current no-smoking policies, past 7-day exposure to tobacco and cannabis, and attitudes toward smoke-free policies and indoor use of tobacco and cannabis [16,23,25,53].

*Measures related to voluntary smoke-free home adoption.* We will ask whether participants voluntarily adopted a smoke-free home in the past 90 days and the length of the last adoption, which will be used to define our primary outcome. Those who report a smoke-free home will be asked how many days they were smoke-free in their home in the past 90 days. Among those who report using cannabis indoors, we will explore whether participants voluntarily adopted a cannabis-free home and the length of time their homes were cannabis-free [16,23].

*Expenditures for tobacco use.* We will obtain information on the amount of money spent on tobacco in the prior week, which we will use to estimate tobacco-related expenditures [23].

*Chronic diseases.* Using the National Health Interview Survey, we will ask about diagnoses of liver disease, renal disease, heart disease, hypertension, diabetes, cancer, pulmonary disease, arthritis, hepatitis C and HIV [54].

*Mental health.* We will screen for depression using the 10-item Center for Epidemiologic Studies Depression Scale [55], anxiety using a seven-item anxiety scale (Generalized Anxiety Disorder-7) [56], and post-traumatic stress disorder (PTSD) using the Primary Care PTSD Screen [57].

*Alcohol and substance use disorders.* We will ask participants about lifetime use of opioids, methamphetamines, crack/cocaine, and cannabis, and for those who report lifetime use, we will ask about use in the past 30 days and number of days used in the past 30 days. To assess cannabis use, we will administer the Cannabis Use Disorders Identification Test-Revised (CUDIT-R) [58]. To assess risky alcohol use, we will administer the Alcohol Use Disorders Identification Test (AUDIT-C) [59,60].

*Satisfaction and usefulness of the intervention* For intervention recipients, at 3- and 6-month follow-ups, we will evaluate satisfaction with the intervention using questions with Likert responses and usefulness using a previously validated item, ‘In the past three months, what role did the intervention play in helping you quit smoking?’

*Exposure to lay health worker coaching* At the 3- and 6-month follow-ups, we will ask residents whether they had any coaching encounters with lay health workers, the number of these encounters, whether they were asked and advised to quit by lay health workers, and the satisfaction and usefulness of these encounters.

*Evaluating the potential for cross-contamination* At the 3- and 6-month follow-ups, we will ask participants who received the intervention whether they had discussed the intervention or shared materials with family and neighbors in their building.

*Cost data.* We will collect data on costs through publically available data (e.g., average sales price of cigarettes, CPT code for cessation services and cost, average time for cessation services) and study business ledger (e.g., intervention start-up material cost, training cost). We will collect and analyze lay health worker time use in the intervention through a time and motion study [61].

### Lay health worker questionnaire measures

*Sociodemographics.* At baseline, we will ask lay health worker participants to provide their age, gender identity, race/ethnicity, role in the facility, and smoking history (if applicable).

*Smoking knowledge and attitudes.* Lay health workers will complete the Smoking Knowledge Attitudes Practices (SKAP) survey at baseline, 3 and 6 months [62,63]. The SKAP survey assesses knowledge, attitudes, barriers, efficacy, and practices related to providing tobacco treatment [63].

*Smoke-free policies.* At baseline, we will ask lay health workers about policies around smoking at the site (e.g., policies restricting tobacco, indoor use of e-cigarettes and/or cannabis, provision of on-site cessation services), enforcement of smoke-free policies (complaints, warnings, or evictions), and barriers to enforcement of current policies.

*Contact with resident participants.* Lay health workers will complete a monthly assessment form that documents attempts to reach resident participants, an assessment of resident participants’ readiness to quit, and an action plan.

### Qualitative Interviews

We will use qualitative interviews to evaluate implementation outcomes of adaptability, scalability, and sustainability of the intervention mapped onto the CFIR domains. We will assess the degree to which the intervention was adopted across sites, how the intervention was implemented, and factors associated with scalability and sustainability [35,64]. We will: (a) identify characteristics of high and low adopters of the intervention at the individual and site levels; (b) examine whether there were differences in engagement in the intervention by language of administration of study components; (c) explore the adaptability of the intervention across subsidized housing sites including features of the intervention that did or did not work; (d) explore satisfaction with the intervention; (e) explore scalability of the intervention by leveraging bilingual housing staff to deliver the linguistically-tailored intervention; and (f) evaluate sustainability of the intervention including payment structures to support housing staff to adopt lay health worker roles.

### Outcomes and Analysis

#### Resident outcomes.

*Primary outcome.* The primary outcome is the percentage of participants with self-reported voluntary adoption of smoke-free homes for 90 days or more at the 6-month follow-up. We will ask participants to place a nicotine sampler in their units to better assess their environmental tobacco exposure at 6-months follow-up [17,65].

*Secondary outcome.* The secondary outcome is the percentage of participants with carbon monoxide verified point prevalence tobacco abstinence at the 6-month follow-up (expired carbon monoxide <5 ppm is defined as abstinence) [66].

#### Other outcome measures.

In addition, we will assess the percentage of participants adopting a cannabis-free home among cannabis users at a 6-month follow-up.

#### Lay health worker outcome.

The primary outcome of interest for lay health worker staff is a change in SKAP score from baseline to the 6-month follow-up.

#### Power and sample size.

The sample size calculation was based on the primary outcome of smoke-free home adoption of at least 90 days at the 6-month follow-up. We also conducted power calculations for the secondary outcome of point prevalence tobacco abstinence at the 6-month follow-up. Power analyses assumed 80% power; intra-cluster correlation of 0.01, two-tailed alpha = 0.05; and 75% retention at 6 months follow-up. With these parameters, we will need N = 544 residents, recruited from 48 housing sites to detect a group difference of 11.5% for the primary outcome of smoke-free home adoption, with 12% for the control arm versus 23.5% for the intervention arm (OR=2.25). For the secondary outcome of point prevalence abstinence at 6 months, the sample size provides 86.6% power to detect a group difference of 11% (13% versus 4%).

#### Statistical analyses.

We will estimate means, standard deviations, frequencies, proportions, and 95% confidence intervals for demographics (age, gender, race/ethnicity, education), other covariates (family size, health condition, insurance), and smoking-related variables (smoking history) at baseline by randomized groups. We will assess whether the variables are balanced at baseline by randomization (randomization check) and attrition (attrition analysis). Instead of using data from completed residents only, we will use all available data from all randomized residents in analyses while assuming that data are missing at random, conditional on observed variables. Multiple imputation will be used for sensitivity analyses with various assumptions on the missing mechanism [67–69].

Primary analysis will assess the intention-to-treat (ITT) effect of the intervention on adopting a smoke-free home compared to the control. The ITT approach will include all the randomized residents, including dropouts and noncompliers to the intervention, in the analysis. Specifically, a generalized linear mixed-effect model with logit link will be used to evaluate the group difference over time, with group (intervention vs. control), time (baseline, 3, and 6 months), and time*group interaction in fixed effects, and housing sites and residents in random effects (random intercept and/or slope). The corresponding group contrast at 6 months and its 95% confidence interval will be estimated. The 3-level data structure —including the housing site, residents, and repeated assessments — will be accommodated by the logistic mixed effects model with random intercepts for sites and residents.

We will conduct several secondary analyses. First, we will fit a generalized mixed-effects logistic model of the secondary outcome, point prevalence abstinence, similarly to the primary analysis. Second, participants lost to follow-up will be compared to those who completed the study to assess whether there are systematic differences in baseline covariates between the two groups. Third, we will include sex, race/ethnicity, and their interactions with the group and time in the logistic mixed effects model to examine any sex and/or race/ethnicity differences in the intervention effects on the outcomes. Fourth, we will perform mediation analyses to identify the mechanisms/pathways by which the intervention may have impacted smoke-free home adoption or point prevalence abstinence outcomes, including knowledge and skills to adopt a smoke-free home, change in smoke-free policy attitudes, exposure to lay health workers, neighborhood environment, and fidelity of intervention delivery. Fifth, we will explore the moderation effects of children or pets at home, indoor cannabis use, or other combustible tobacco use on intervention outcomes of smoke-free homes and point prevalence abstinence outcomes via mixed effects regression models. Replicability of within-group changes on primary and secondary outcomes will be tested by comparing baseline to 6-month changes in the intervention group to corresponding 6- to 12-month changes in the waitlist control group.

Analyses of lay health worker data will include a pre-post training analysis of the smoking knowledge, attitudes, practices, efficacy, and barriers scales (SKAP) using generalized mixed linear models. We will fit generalized mixed linear regression models to examine factors associated with a change in each of the scales, accounting for correlations due to clustering by sites and residents and adjusting for demographics, geographic location, lay health worker smoking status, coaching encounters with residents, and lay health worker job role.

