### Randomization

The study will be conducted in 48 affordable housing sites across Northern California. We will use the method of restricted randomization—commonly applied in cluster-randomized trials and used in our previous trial—to ensure an acceptable level of balance across groups at baseline [25,33]. Our goal is to achieve balance for the following variables: property size (i.e., number of residents), smoking-related policies (e.g., existing smoke-free policies), and geography (e.g., location). First, we will create two sets of 24 housing sites, each balanced on these variables. Second, we will randomly assign one set of sites to the intervention and the other to wait-list control.

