### Participants and setting

#### Resident participants.

We aim to recruit N = 544 resident participants, n = 272 each in the intervention and wait-list control arms. To be eligible, resident participants must: (1) identify as current smokers (smoked at least 100 cigarettes in their lifetime and smoke at least 5 cigarettes per day, verified by expired carbon monoxide [CO] ≥ 5 parts per million [ppm]) (41); (2) smoke in their home; (3) expect to live in the same housing site for at least 12 months; (4) be at least 18 years old; (5) speak Chinese, English, Spanish, or Vietnamese; (6) be able to meet with the study staff for followup visits; and (7) be able to provide informed consent. Exclusion criteria include a contraindication to study-related procedures or assessment (e.g., unable to provide informed consent).

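### The primary model leaves out the three site variables that restrict the randomisation and all baseline predictors, so its intervals are slightly too wide and its missing-at-random assumption rests on few variables

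*Protocol article*

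**What the plan says.** The Randomization section names what the allocation is to balance: "property size (i.e., number of residents), smoking-related policies (e.g., existing smoke-free policies), and geography (e.g., location"). It gives the procedure as "First, we will create two sets of 24 housing sites, each balanced on these variables", after which one set is assigned at random to each arm.

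Under Statistical analyses the primary model is written out term by term: "Specifically, a generalized linear mixed-effect model with logit link will be used to evaluate the group difference over time, with group (intervention vs. control"). The remaining terms are listed as "time (baseline, 3, and 6 months), and time*group interaction in fixed effects, and housing sites and residents in random effects". No site-level or resident-level covariate is listed. Covariates are named elsewhere: sex and race/ethnicity in a secondary model, several moderators in another, and demographics and geographic location in the staff analysis.

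On missing data, all available data are used while "assuming that data are missing at random, conditional on observed variables". The article adds: "Multiple imputation will be used for sensitivity analyses with various assumptions on the missing mechanism". Attrition is compared on baseline covariates. Eligibility requires that residents "2) smoke in their home", and 75% retention is expected at 6 months.

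**The concern.** There are two linked gaps.

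**Design and analysis do not match.** When allocation is forced to balance on a site variable, the variation which that variable explains largely drops out of the difference between arms. A model that omits the variable still counts that variation in its site variance and so in its standard error. Intervals come out too wide and the test rejects too rarely. An existing smoke-free policy is a plausible predictor of adopting a smoke-free home, so the omitted variables may carry information.

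**The missing-at-random assumption is wider than the model.** A likelihood analysis is protected only for dropout that depends on what the model contains. Here that is arm, site, time and the resident's own outcomes. Everyone smokes at home on entry, so the baseline outcome says nothing about who will adopt or drop out. If heavier dependence predicts both dropout and failure to adopt, and does so differently by arm, the primary estimate is exposed although dependence is measured.

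**Working it through.** **Inputs from the article.** 544 residents, 48 sites, 75% retention, ICC 0.01, two-sided alpha 0.05, adoption 12% versus 23.5%. Retained: 544 × 0.75 = 408, or 204 per arm and 408/48 = 8.5 per site.

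**The plan's own sample size.** A continuity-corrected comparison of 12% with 23.5% at 80% power needs 190 per arm. Design effect: 1 + (8.5 − 1) × 0.01 = 1.075. Total: 2 × 190 × 1.075 / 0.75 = 544.7, against 544 stated. The calculation reproduces and, like the model, uses no covariates.

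**Effect of omitting the balanced variables.** Let R² be the share of between-site variance that they explain. The article does not give R², so it is an assumption. With perfect balance:

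- variance the model assumes: D = 1 + 7.5 × ICC
- variance of the contrast under restriction: T = 1 + 7.5 × ICC × (1 − R²)
- true type I error = 2 × [1 − Φ(1.96 × √(D/T))]
- power with s = √[(0.12 × 0.88 + 0.235 × 0.765)/204] = 0.0374: unadjusted Φ[(0.115 − 1.96 s√D)/(s√T)], adjusted Φ[0.115/(s√T) − 1.96]

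| ICC | R² | D | T | √(D/T) | Type I error | Power, unadjusted → adjusted |
|---|---|---|---|---|---|---|
| 0.01 (plan) | 0.5 | 1.075 | 1.0375 | 1.018 | 4.6% | 84.7% → 85.5% |
| 0.01 (plan) | 1 | 1.075 | 1 | 1.037 | 4.2% | 85.1% → 86.8% |
| 0.05 (assumed) | 0.25 | 1.375 | 1.281 | 1.036 | 4.2% | 75.4% → 77.5% |
| 0.05 (assumed) | 0.5 | 1.375 | 1.1875 | 1.076 | 3.5% | 76.2% → 80.6% |
| 0.05 (assumed) | 1 | 1.375 | 1 | 1.173 | 2.2% | 78.1% → 86.8% |

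**Check by simulation.** The set-up was 48 sites with about 8.5 retained each, allocation chosen as the best balanced of 60 draws on three invented site covariates, weighted site-level regression with and without them, and 4000 runs per cell (Monte Carlo standard error of type I error about 0.34 points). This approximates the logistic mixed model and does not fit it.

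| ICC | R² | Type I error, unadjusted → adjusted | Standard error | Power |
|---|---|---|---|---|
| 0.01 | 0.5 | 3.9% → 4.6% | 0.0384 → 0.0381 | 84.1% → 83.9% |
| 0.01 | 1 | 4.8% → 5.4% | 0.0386 → 0.0377 | 84.4% → 85.2% |
| 0.05 | 0.5 | 3.6% → 4.6% | 0.0426 → 0.0403 | 74.2% → 77.2% |
| 0.05 | 1 | 2.1% → 4.6% | 0.0427 → 0.0376 | 75.7% → 84.3% |

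At the planned ICC the standard error is 1-2% too large and power changes by −0.2 to +0.8 points.

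**Missing data, with assumed figures.** Take a binary baseline predictor split evenly. Adoption is 6% and 18% in its two levels in controls (mean 12%) and 12% and 35% under intervention (mean 23.5%). Retention is 75% in both levels in controls, and 65% and 85% under intervention. Observed intervention rate: (0.65 × 0.12 + 0.85 × 0.35)/1.5 = 25.0%. The observed difference is 13.0 points against a true 11.5. With no true effect, the same retention gives (0.65 × 0.06 + 0.85 × 0.18)/1.5 − 0.12 = 0.8 points. If controls show the reverse pattern (85% and 65%), it gives 12.8% − 11.2% = 1.6 points.

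**The case against.** The strongest reply is that this is a refinement. The only ICC in the article is 0.01, where the effect is barely visible. Higher ICCs and every value of R² are assumptions, and R² = 1 is an extreme. The formula supposes perfect balance, while the article promises only an acceptable level. All of this stands and limits the size of the point.

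A reader might infer that the primary intervals are invalid or that false positives are inflated. The documents do not support that. The random site intercept absorbs the omitted site variance, and the error runs in the conservative direction.

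A reader might also infer that the missing-at-random assumption conditions on almost nothing and that the analysis is in effect one of completers by arm. That goes too far. Arm and site are in the model, residents lost after month 3 contribute their 3-month outcome, and multiple imputation under several mechanisms is planned, as is an attrition comparison. The imputation covariates may properly be left to an analysis plan. What remains is that imputation is only a sensitivity analysis and the primary model holds no baseline predictor. The 3-month outcome may also help little: if it uses the same 90-day definition, only those who adopted almost at once after enrolment can meet it by then.

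Finally, it is tempting to argue that residents are recruited after their site's arm is known, so that the arms differ at entry. The only basis is the word order of the Fig 1 caption, and that figure is not shown. The Randomization and Recruitment sections do not state the sequence, so this point does not rely on it.

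**Conclusion.** The point holds as a modest mismatch between design and analysis. The written primary model omits the three restriction variables, which makes intervals slightly too wide and the test slightly conservative. At the planned ICC of 0.01 the consequence is negligible. It becomes material only if the ICC is higher and size, policy or location predicts adoption. One feature adds some weight: if the two sets of 24 are fixed before a single assignment, only two allocations are possible and inference rests on the model, which is a further reason to include the design variables.

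The missing-data part does not depend on the ICC. The article invokes observed variables that its primary model does not contain, with a quarter of residents expected to be lost. The possible bias cannot be sized from the documents. The 0.8 to 1.6 points above illustrate it under invented retention patterns and are not an estimate for this trial. The stated sample size of 544 is unaffected.

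**What to change.** Add property size, existing smoking-related policy and geography as fixed effects in the primary model. Add a very short prespecified list of baseline predictors of outcome and dropout that the questionnaire already covers, for example the nicotine dependence score. Use the same variables in the planned multiple imputation. Keep the unadjusted model as a sensitivity analysis.

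The costs are small but not nil. With size as one term, policy as yes/no and geography as three counties (the coding is an assumption), adjustment uses 1 + 1 + 2 = 4 of the 48 − 2 = 46 site-level degrees of freedom. About 204 × 0.12 + 204 × 0.235 = 72 adopters are expected among those retained, so the covariate list must stay short. The odds ratio also becomes conditional on the covariates, so the standardised (marginal) risk difference at 6 months should be reported beside it. Recruitment was under way when the article was submitted and the change needs no new data. It should be fixed in writing before outcomes are examined by arm.

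### The primary logistic mixed model treats baseline as an outcome occasion, yet eligibility fixes that outcome at zero, so its baseline and baseline-referenced interaction terms have no finite estimate

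*Protocol article*

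**What the plan says.** The Statistical analyses section gives the primary model as a logistic mixed model with group, "time (baseline, 3, and 6 months), and time*group interaction in fixed effects, and housing sites and residents in random effects". The quantity to be reported is stated next: "The corresponding group contrast at 6 months and its 95% confidence interval will be estimated". The repeated-measures structure is to be "accommodated by the logistic mixed effects model with random intercepts for sites and residents".

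The outcome in that model is "self-reported voluntary adoption of smoke-free homes for 90 days or more at the 6-month follow-up" (Resident outcomes). The eligibility list under Resident participants includes "2) smoke in their home".

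For the secondary outcome, the protocol says "we will fit a generalized mixed-effects logistic model of the secondary outcome, point prevalence abstinence, similarly to the primary analysis". Smoking status at entry must be "verified by expired carbon monoxide [CO] ≥ 5 parts per million [ppm"), while at follow-up "expired carbon monoxide <5 ppm is defined as abstinence".

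The Power and sample size section plans for 12% versus 23.5% at 6 months (OR 2.25), with a site intra-cluster correlation of 0.01 and 75% retention. No resident-level variance is given.

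**The concern.** A person who currently smokes at home cannot at that moment have kept a smoke-free home for 90 days or more. Enrolment therefore fixes the primary outcome at 0 for every resident in both arms at baseline. The CO criteria do the same for abstinence. A logistic model with separate baseline cells for the two arms is then asked to estimate two log odds from cells with no events.

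This is not detail left for an analysis plan. The article names the time points, the interaction and the random effects, and they conflict with its own entry criteria. If analysts discover this only when the model misbehaves on trial data, they must choose a repair to the primary analysis after seeing those data.

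A second issue sits in the same sentence. The model carries a resident random intercept, so its 6-month odds ratio is conditional on resident and site, whereas the planning odds ratio of 2.25 compares two population proportions. Readers will be inclined to set the two side by side.

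**Working it through.** **1. The planning figure.** The odds ratio is (0.235/0.765)/(0.12/0.88) = 2.25, as printed. Two proportions, two-sided 0.05, 80% power, continuity-corrected: 190 per arm. Completers per site: 544 x 0.75/48 = 8.5. Design effect: 1 + 7.5 x 0.01 = 1.075. Then 190 x 1.075 = 204.25, rounded up to 205; 205/0.75 = 273.3, rounded up to 274 per arm, 548 in total. The stated 544 gives 204 completers per arm and 80.15% power. The plan's figure reproduces, and it rests on marginal proportions with a site effect only.

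**2. Why there is no finite maximum.** With baseline logit b and combined random effects u, a baseline row with outcome 0 contributes 1/(1 + exp(b + u)) to the likelihood. For every u this rises towards 1 as b falls, so the likelihood always improves by lowering b. In the limit the row contributes a factor of 1 and drops out, leaving the likelihood of the 3- and 6-month rows. The 6-month contrast therefore tends to the value from the model without baseline.

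**3. Numerical check.** Three simulated trials were fitted with site and resident intercepts and time as categories. From the protocol: 544 residents, 48 sites, 12% and 23.5% at 6 months, 75% retention. Assumed, because the protocol gives no figures: resident SD 1.8, site SD 0.18 (latent ICC about 0.01), 3-month rates 6% and 13%, 3-month retention 80%.

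In trial 1 the profile log-likelihood was -325.08 at b = -3, -296.62 at -5, -287.14 at -8, -285.86 at -12, and -285.83 at -20 and below. The other two trials behaved alike. The 6-month log odds ratios were:

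| | Trial 1 | Trial 2 | Trial 3 |
|---|---|---|---|
| No baseline rows | 1.7275 | 0.7101 | 1.2837 |
| b = -20 | 1.7275 | 0.7101 | 1.2837 |
| b = -12 | 1.7210 | 0.7085 | 1.2794 |
| b = -8 | 1.5880 | 0.6661 | 1.1795 |
| b = -5 | 1.2974 | 0.5446 | 0.9445 |
| Ratio, b = -5 to no baseline | 0.75 | 0.77 | 0.74 |

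A fit driven far enough down recovers the right contrast. A fit held at -5 gives a log odds ratio 23% to 26% too small.

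**4. What reference coding does.** With baseline as reference, the 6-month contrast is the group coefficient (the difference between two divergent baseline logits) plus the 6-month interaction. From the free fits:

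| | Trial 1 | Trial 2 | Trial 3 |
|---|---|---|---|
| Baseline logit, control | -80.22 | -114.02 | -51.15 |
| Baseline logit, intervention | -82.45 | -110.65 | -51.32 |
| Group coefficient (difference) | -2.24 | 3.37 | -0.17 |
| 6-month interaction | 3.96 | -2.66 | 1.46 |
| Sum: 6-month contrast | 1.73 | 0.71 | 1.28 |

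The interaction takes either sign according to where the optimiser stopped, while the sum stays put. Approximate standard errors of the baseline logits were 36 to 7,151.

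**5. The scale of the odds ratio.** For a random-intercept SD s, solve for logits a0 and a1 at which the inverse logit of (a + sZ), averaged over standard normal Z, equals 0.12 and 0.235. The conditional odds ratio is exp(a1 - a0):

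| SD | 0.18 | 1 | 1.5 | 2 | 3 |
|---|---|---|---|---|---|
| Conditional OR | 2.26 | 2.53 | 2.88 | 3.37 | 4.87 |

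A site effect alone (SD 0.18) hardly moves it; the resident intercept does. In the three trials, the fits without baseline rows gave odds ratios of 5.63, 2.03 and 3.61 against raw marginal ones of 2.96, 1.55 and 2.15. Dropping baseline alone does not close this gap.

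**The case against.** The strongest reply is that the protocol reports only the 6-month group contrast, and that contrast survives. This stands, and it rules out a reading that a reader might draw: that the primary odds ratio does not exist or is wrong because of the baseline rows. The agreement is a limiting result for categorical time and random intercepts. In simulations with assumed 3-month rates as low as 2% and 4%, a minority of fits with and without baseline rows still differed materially, in trials where the resident SD itself ran very large.

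Non-convergence cannot be asserted as certain either. Across simulations, reported convergence with baseline rows ran from 35% of trials with one optimiser to 100% with a bounded one. The article names no software, so no rate can be attached to this trial.

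A reader might also infer that baseline inflates the odds ratio away from 2.25, or that the trial loses its power. The documents support neither. The gap arises from the resident intercept and appears equally without baseline rows. Conditional and marginal odds ratios share the same null, and in small simulations (25 trials per scenario) rejection rates for the mixed model were 88% and 92%, with or without baseline, against 84% and 88% for a simple comparison of proportions.

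Nor can it be said that the 3-month outcome must be almost all zeros. Coaching takes place at enrolment, visits may be completed up to a month late, and no 3-month rate is given.

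What the reply does not remove is that a stated model conflicts with stated eligibility, and that its printed baseline and interaction coefficients would be meaningless.

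**Conclusion.** The point holds in a limited form. As specified, both the primary and the abstinence models include an occasion at which the outcome is 0 by design, so the baseline and baseline-referenced interaction terms have no finite maximum-likelihood estimate. The 6-month contrast is recoverable. The risk is practical: convergence warnings, unreliable standard errors, or a contrast shrunk by about a quarter if an early stop or a penalty holds the baseline logit near -5 (much less at -8, negligible at -12).

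The odds-ratio scale is a separate matter with a separate cause. For assumed resident SDs of 1 to 3, the planned difference corresponds to a conditional odds ratio of about 2.5 to 4.9. An odds ratio of that size would not mean that the trial exceeded its plan.

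These conclusions assume time as three categories, normal random intercepts, and entry criteria applied as written. A few contradictory self-reports at baseline would make the estimates finite, but they would be data errors. The shrinkage figures depend on the simulation inputs in step 3 of the working.

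**What to change.** Remove baseline from the outcome vector in the primary and abstinence models, and in the sex and race/ethnicity interaction models that extend them. Model post-baseline occasions only: 3 and 6 months as categories, with group, time, their interaction, and random intercepts for site and resident. This keeps the likelihood-based use of all available follow-up data under missing at random.

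From that model, report the 6-month marginal risk difference and odds ratio, standardised over the random effects, each with a 95% CI. The result can then be set against 12% versus 23.5%. If the conditional odds ratio is also shown, label it as such.

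A model of 6 months alone with a site effect is an acceptable alternative. It drops the resident intercept, but 3-month data would then inform missing 6-month outcomes only through imputation, which the protocol reserves for sensitivity analyses. That is a trade-off and is not required.

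The cost is wording and the standardisation step. No new data are needed, because the baseline rows carry no outcome information. Data collection is planned to run to the end of December 2026, so the change can be made before the analysis.
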